## STUDY SYNOPSIS

|                            |                                                                                                                                                                                                                              |
|----------------------------|------------------------------------------------------------------------------------------------------------------------------------------------------------------------------------------------------------------------------|
| Study Title:        | Immediate Breast Reconstruction with and without the use of Acellular Dermal Matrix - A Randomized Controlled Trial                                                                                                          |
| Short title:        | ADM Strattice™ Breast Trial                                                                                                                                                                                                  |
| Study design:       | A randomized controlled multicentred trial, comparing Immediate Breast Reconstruction (IBR) without (group A) and with (group B) the use of Acellular Dermal Matrix (Strattice™), in the setting of breast cancer treatment. |
| Study population:   | Patients with breast cancer who are having a planned mastectomy and Immediate Breast Reconstruction with implants. The study will aim to recruit 120 patients from 5 centres across the UK and Sweden.                       |
| Primary objective:  | The purpose of this study is to evaluate the effectiveness of Acellular Dermal Matrix (Strattice™) in post-mastectomy Immediate Breast Reconstruction (IBR) with implants, in the setting of breast cancer treatment.        |
| Primary outcome:    | The primary outcome measure is a comparison of the number of unplanned surgical breast procedures for each patient between the two treatment arms.                                                                           |
| Secondary outcomes: | 
 
• Aesthetic outcome
 
• No. of surgical procedures
 
• Complications
 
• Cost-Benefit analysis
 
                                                        |

|                        |                                                                                                                 |
|------------------------|-----------------------------------------------------------------------------------------------------------------|
|                        | 
 
• Quality of Life
 
                                             |
| Study duration: | 24 months total study duration. Study duration for each patient will be 24 months from time of initial surgery. |

86

87

88

89

## TRIAL SCHEMA

[figure not shown]

## SCHEDULE OF EVENTS

|                                        | Screening | Visit 0
Baseline | Surgery /
Post-op  | Visit 1
(1-4 weeks) | Visit 2
(3 months) | Visit 3
(6 months) | Visit 4
(12 months) | Visit 5
(24 months) |
|----------------------------------------|-----------|---------------------|-----------------------------------|------------------------|-----------------------|-----------------------|------------------------|------------------------|
| PIS provided                           | x         |                     |                                   |                        |                       |                       |                        |                        |
| ICF signed                             | x         |                     |                                   |                        |                       |                       |                        |                        |
| Patient randomised                     | x         |                     |                                   |                        |                       |                       |                        |                        |
| Eligibility checked                    | x         | x                   |                                   |                        |                       |                       |                        |                        |
| Medical history                        |           | x                   |                                   |                        |                       |                       |                        |                        |
| Clinical examination /
measurements |           | x                   | x                                 | x                      | x                     | x                     | x                      | x                      |
| Drain removed                          |           |                     |                                   | x                      |                       |                       |                        |                        |
| Photographs taken                      |           | x                   |                                   |                        | x                     | x                     | x                      | x                      |
| Case Report Form (CRF)                 |           | x                   | x                                 | x                      | x                     | x                     | x                      | x                      |
| QoL Questionnaire -
EORTC QLQ-C30   |           | x       |                                   |                        |                       | x                     | x                      | x                      |
| QoL Questionnaire –
EORTC BR23      |           | x       |                                   |                        |                       | x                     | x                      | x                      |
| QoL questionnaire –
EORTC BRR26     |           |                     |                                   |                        |                       | x                     | x                      | X                      |
| Adverse Events                         |           |                     | x                                 | x                      | x                     | x                     | x                      | X                      |

 – Baseline QoL questionnaires should be completed before randomization

 – Patients undergoing single-Stage direct to implant IBR will have one surgical visit. Patients undergoing two-stage IBR with expander will attend two separate surgical visits.

## ABBREVIATIONS

| Abbreviation | Explanation                                                |
|--------------|------------------------------------------------------------|
| ADM          | Acellular Dermal Matrix                                    |
| AE           | Adverse Event                                              |
| BCS          | Breast Conserving Surgery                                  |
| CC           | Capsular Contracture                                       |
| CRF          | Case Report Form                                           |
| EORTC        | European Organisation for Research and Treatment of Cancer |
| GCP          | Good Clinical Practice                                     |
| IBR          | Immediate Breast Reconstruction                            |
| ICF          | Informed Consent Form                                      |
| IP           | Intellectual Property                                      |
| ISF          | Investigator's Site File                                   |
| MDT          | Multi-disciplinary Team Meetings                           |
| NHS          | National Health Service                                    |
| NRES         | National Research Ethics Service                           |
| OUH          | Oxford University Hospitals                                |
| PIS          | Patient Information Sheet                                  |
| PMM          | Pectoralis Major Muscle                                    |
| QoL          | Quality of Life                                            |
| R&D          | Research and Development                                   |
| REC          | Research Ethics Committee                                  |
| RT           | Radiotherapy                                               |
| SAE          | Serious Adverse Event                                      |
| SMF          | Sub-mammary fold                                           |
| SSDL         | Site Signature and Delegation Log                          |
| TE           | Tissue Expanders                                           |
| TRAM         | Transverse Rectus Abdominis Musculocutaneous               |
| UK           | United Kingdom                                             |

|     |                                               |                                     |
|-----|-----------------------------------------------|-------------------------------------|

### 3 BACKGROUND AND TRIAL RATIONALE

Despite the availability of Breast Conserving Surgery (BCS), removal of the breast is performed in 40-50% of breast cancer patients. There has been a growing demand for breast reconstruction, particularly as an Immediate Breast Reconstruction (IBR) at the time of the mastectomy rather than a delayed procedure after mastectomy. IBR after mastectomy has its advantages over delayed, as it is possible to keep more of the native skin envelope intact, and as such, creating a more natural shape. It also carries psychological benefits for women .

In broad terms, there are three different techniques in breast reconstruction available: (1) Tissue expander/implant reconstruction. (2) Pedicled flaps with or without an implant. (3) Transfer of abdominal fat in the form of a transverse rectus abdominis musculocutaneous or TRAM flap, or (today more commonly) as a free perforator flap using the same abdominal skin and fat but no muscle, based on deep inferior epigastric perforator vessels (DIEP). Other alternatives, but less common, are free flaps using buttock or thigh fat (SGAP Flap). Tissue expander/ implant reconstruction remains the most common method, especially in the setting of IBR .

Two variations of the technique for IBR with implants can be applied: The partial muscle coverage (dual plane) and the full submuscular technique. With partial muscle coverage the implant is placed under the pectoralis major muscle (PMM), which leaves the inferior and lateral part of the implant with skin and subcutaneous tissue coverage only. With full muscle coverage, the implant is completely covered by the PMM, anterior rectus fascia and usually a serratus anterior muscle flap. Full submuscular coverage has traditionally been recommended to prevent direct contact between the implant and the mastectomy skin flaps, but can result in an implant positioned too high and at times a more difficult lower pole expansion with a less defined submammary fold (SMF), compared with placing the implant in a partial subcutaneous position (dual-plane) . It also requires a more extensive muscle dissection, with longer operating time. The partial muscle technique also has its limitations with migration of implant, bottoming out, malposition, as well as implant visibility and palpability .

Prosthetic breast reconstruction has drawbacks, where capsular contracture (CC) remains the most common problem. CC can severely impair the aesthetics of the reconstruction and give patients discomfort. CC is especially problematic in patients receiving adjuvant radiotherapy (RT), and with few exceptions, these patients need further surgical revisions, and on occasion conversion to autologous flap procedures. Currently about 40% of the patients receive postmastectomy RT at our institutions.

The incidence of CC reported in the literature ranges from 15%-100% in the presence of adjuvant RT. The occurrence of CC is unpredictable and revision surgery such as capsulotomy or capsulectomy may not prevent its recurrence. In the long term, this creates a high incidence of reoperations for implant-based reconstructions, especially in the presence of RT, to maintain an acceptable aesthetic appearance and also comfort of the reconstructed breast. The incidence of revision surgery reported in the literature greatly varies, where some studies report a reoperation rate as high as 70%. Over the years, with the introduction of different skin-sparing and nipple-sparing mastectomy techniques, coupled with better implant devices, there has been an improvement in the aesthetic results of prosthetic breast reconstruction. However, the rate of reoperation remains high.

To utilize the benefits of the dual-plane technique, perform more reconstructions as a single-stage procedure without tissue expansion, and overcome the drawbacks of using full muscle coverage, Acellular Dermal Matrix (ADM) in implant-based breast reconstruction was introduced in 2003. ADM is a biological product with different origins, depending on the manufacturer. This study will be using Strattice™, an ADM product marketed by Lifecell™ EMEA Limited derived from porcine dermis. The dermal tissue undergoes several processes to reduce antigens, remove cells and DNA, while maintaining an intact extracellular matrix (ADM). The remaining matrix allows for vascular ingrowth and integration into host tissue.

The use of ADM has quickly gained acceptance, with the following benefits reported in the literature: decreasing or eliminating the need for tissue expanders (TE), improved aesthetic outcome, increased initial fill volumes of TE, fewer expansions, decreased rate of revision surgery and reoperations, decreased incidence of CC, better control of SMF, faster time to completion of reconstruction, improved lower pole expansion, and reduced costs.

There is supporting evidence for improved aesthetic outcome  from several case series without comparison groups, with personal opinions and no data, and from single surgeons. Supporting evidence for decreasing or eliminating the need for tissue-expanders (TE) also comes from several review articles. 

For decreased rates of revision surgery there is some supporting evidence, as well as for decreased incidence of capsular contracture. 

As for improved lower pole expansion, there is no data. There are some articles supporting the evidence of reduced costs for an implant reconstruction .

One concern for using ADM in IBR is the possibility of complications. There is some conflicting data on the actual complications rates, and recent reports suggests a higher incidence of flap necrosis, seroma and infection.  Other groups report a complication rate similar to IBR without ADM.  A recent review and meta-analysis paper by Ho et al also suggests a significantly higher rate of complications, such as flap necrosis.  However, there is currently no data from any prospective randomized trials that supports the above described advantages or disadvantages.

## 4 STUDY SETTINGS

Currently in Oxford, most patients receiving Immediate Breast Reconstruction (IBR) using implants will undergo a two stage post-mastectomy reconstruction involving an initial procedure to fit a tissue expander and then a second surgery to replace the tissue expander with a permanent breast implant. This study will compare this standard treatment option with the additional use of ADM (Strattice™) as surgical mesh reinforcement.

Strattice™ Tissue Matrix is a porcine dermis-derived biologic (pig skin) surgical mesh used in surgery to help support the lower outer part of the breast, providing a scaffold, or framework, which allows the body's own cells and blood vessels to grow into it. It gradually becomes part of the body as over time Strattice™ is replaced by the body's own tissue. Strattice™ Tissue Matrix itself contains no human cells. Strattice™ has been indicated for use in post-mastectomy breast reconstruction with implant since 2008 and carries a CE mark, which means it has been approved for use in the European Economic Area (EEA). It is not an experimental product. Strattice™ is marketed by LifeCell™ EMEA Ltd. who are providing the product free of charge for this study.

Strattice™ is routinely used in breast reconstruction in some European countries, including in the UK, but is not routinely available for patients undergoing treatment for breast cancer in Oxford University Hospitals (OUH) NHS Trust due to cost implications. The results of this study may support a case for the routine use of the product if the cost of the product is offset by the reduction in number of subsequent operations or reduced hospital visits. The study will evaluate the two treatment arms in terms of effectiveness, safety and efficacy endpoints as well as economic considerations.

## **5 TRIAL DESIGN AND METHODOLOGY**

The study is a randomized controlled multicentred trial comparing Immediate Breast Reconstruction (IBR) without (Group A) and with (Group B) the use of ADM (Strattice™). Participants eligible for the study are women with breast cancer who are having a planned mastectomy and IBR with implants.

### **5.1 Study population**

The study will aim to recruit 120 patients from 5 different sites across the UK and Sweden: Karolinska University Hospital (Sweden), Capio St. Görans Hospital (Sweden), Danderyds Hospital (Sweden), Södersjukhuset (Sweden), Churchill Hospital (UK)

### **5.2 Study duration**

The total study duration for each patient will be 24 months post initial surgery. The definition of end of study will be the last follow-up visit for the last patient recruited.

### **5.3 Randomisation**

Patients will be allocated to treatment according to permuted block technique. The randomization will be performed using a computer based system located at Regional Cancer Center (RCC) within Karolinska Institutet. The randomization process will be stratified for the participating units, and also for patients treated with neo-adjuvant chemotherapy.

### **5.4 Statistical Methods**

The main endpoint to be analyzed is the proportion of unplanned reoperations after the initial breast reconstruction. The difference in proportions between the two groups will be presented as a difference in proportion together with a 95% confidence interval. Differences will be tested using Fishers Exact Test. Logistic regression will be used to take into account possible confounding factor.

364  
365 The sample size calculation is made with respect to the primary endpoint, which is to  
366 compare the number of unplanned surgical procedures (unanticipated) between IBR  
367 using full muscle coverage without ADM vs. IBR with ADM using partial muscle  
368 coverage (group B) over the study period of two years. The power calculation is based  
369 on a reoperation rate of 60% in the non-ADM group and a reoperation rate of 30% in  
370 the ADM group. The follow-up time is 24 months from the primary operation.

371  
372 To detect a statistical difference between the two groups a total number of 98 patients -  
373 i.e. 50 patients in each arm – is needed, if the significance level is set to 5% and the  
374 power in the study to 80%. To account for a loss to follow-up, a total of 120 patients will  
375 be recruited in the study.

376

## 6 OUTCOMES AND ASSESSMENT OF EFFICACY

### 6.1 Primary outcome measures

The primary endpoint of this study is the number of unplanned/ unanticipated surgical breast procedures. Other endpoints in the trial will be secondary.

As reoperation rates are a relatively objective measure of surgical intervention required to attain and maintain acceptable aesthetics in implant based reconstructions, it will serve as a good primary endpoint for the study. See Appendix 1 for guidance on defining reoperations.

### 6.2 Secondary outcome measures

1. To measure any difference between the two study groups in complication rates.
2. To compare the total number of surgical procedures (planned or unplanned) between the two study groups).
3. To measure the aesthetic outcome between the two study groups using a 6-point scale. The evaluation will be done by three independent groups consisting of lay people, professionals (breast/ plastic surgeons) and patient evaluation. The aesthetic evaluation will be based on the pre and postoperative photos.
4. A cost-benefit analysis comparing the cost for an IBR with implant without ADM, vs. IBR with ADM (Strattice™) during a 24 months follow-up time.
5. Measure Quality of Life in both groups, using the EORTC QLQ-C30 (Generic tool), EORTC-BR23 (Breast cancer specific tool), EORTC-BRR26 (Specific for breast reconstruction)

## 7 ELIGIBILITY CRITERIA FOR PARTICIPANTS

### 5.1 Inclusion Criteria

1. Patient with invasive or pre-invasive (in situ) breast cancer, planned for immediate breast reconstruction post-skin sparing or nipple sparing mastectomy (unilateral or bilateral)
2. Patient agrees to participate in study and to sign an informed consent form
3. Able and willing to return for all scheduled and required study visits

### 5.2 Exclusion Criteria

1. Is a smoker (patient who has quit at least 2 weeks prior to surgery can be included)
2. BMI <18 or > 30
3. Previous radiation therapy to the area at any time (adjuvant or planned therapy is not an exclusion criteria)
4. Insulin-dependent diabetes or any immune deficiency requiring immunosuppressant use such as cortisone or biological therapies
5. Predicted **implant** size <200 or >600 ml per investigator assessment
6. Allergy to porcine or refuses to receive porcine material
7. Pregnancy or lactating
8. Neoadjuvant treatment with chemotherapy (adjuvant or planned therapy is not an exclusion criteria)
9. Patient is unable or unwilling to give informed consent.

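### Randomisation balances no patient-level prognostic factor: the only such stratum is a group the protocol excludes, while planned radiotherapy, which the protocol ties to revision surgery, is left to chance

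*Protocol*

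**What the plan says.** - **Eligibility** (section 7, 5.2 Exclusion Criteria, item 3): the exclusion is "Previous radiation therapy to the area at any time (adjuvant or planned therapy is not an exclusion criteria"). Patients expecting radiotherapy therefore enter. Section 6.7 adds that adjuvant radiotherapy is no ground for withdrawal.
- **Background** (section 3): "Currently about 40% of the patients receive postmastectomy RT at our institutions". Of contracture after adjuvant radiotherapy it says that "with few exceptions, these patients need further surgical revisions".
- **Endpoint** (Appendix 1): capsulotomy, capsulectomy, lipofilling, implant exchange and secondary autologous reconstruction all count as unplanned reoperations, so revisions of that kind are primary-endpoint events.
- **Randomisation** (5.3): "stratified for the participating units, and also for patients treated with neo-adjuvant chemotherapy". Item 8 of the exclusion criteria rules out neo-adjuvant chemotherapy.
- **Analysis and sample size** (5.4): an unadjusted Fisher test, with logistic regression for confounding but no factor named. The power calculation assumes "a reoperation rate of 60% in the non-ADM group and a reoperation rate of 30% in" the ADM group. No source or radiotherapy mix is given for either rate.

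**The concern.** Stratification is meant to balance factors that predict the outcome. Here the one patient-level slot goes to a characteristic that no eligible patient should have. Radiotherapy, the patient-level factor that the background links most directly to revision surgery, is left to chance in a trial of 120.

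An uneven split in radiotherapy would feed into the observed reoperation difference, and the planned Fisher test cannot take it into account. There is also a planning question. If a large share of both arms is irradiated and most irradiated patients are reoperated, a 30% rate under ADM requires a benefit in irradiated breasts too. The protocol does not say that it assumes one.

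**Working it through.** **Inputs.** From the protocol: 60% and 30% reoperation, 5% significance, 80% power, 98 evaluable, 120 recruited (60 per arm), about 40% irradiated. Assumed: a two-sided test; the 40% applies to trial patients; 80-90% of irradiated controls are reoperated (the protocol gives no figure); and, where stated, ADM halves the rate in both groups.

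**1. The plan's own figure.** The two-proportion formula for 60% v 30% gives 42 per arm uncorrected and 49 with continuity correction. 2 x 49 = 98, as stated (the text also says 50 per arm, which is 100). Exact Fisher power at 49 per arm is 81.5%.

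**2. Chance imbalance in radiotherapy share.** SD = sqrt(2 x 0.4 x 0.6 / 60) = 0.089, or 8.9 points. The probability of a difference of 10 points or more is 30.5%. At 49 evaluable per arm the SD is 9.9 points and the probability about 35%.

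**3. Effect on the risk difference.** Non-irradiated control rate = (0.60 - 0.4r)/0.6, where r is the irradiated control rate. Shift = 0.10 x the contrast between irradiated and non-irradiated rates.

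| | r = 80% | r = 90% |
|---|---|---|
| Non-irradiated controls | 46.7% | 40% |
| Contrast in controls | 33.3 points | 50 points |
| Contrast under ADM, rates halved | 16.7 points | 25 points |
| Shift, control contrast only | 3.3 points | 5 points |
| Shift, average of both arms | 2.5 points | 3.75 points |

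The range is therefore about 2.5 to 5 points per 10-point imbalance.

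**4. Precision available from balancing and adjusting.**
- Unadjusted variance, summed over arms: 0.6 x 0.4 + 0.3 x 0.7 = 0.450.
- Within strata, r = 80%: controls 0.4 x 0.8 x 0.2 + 0.6 x 0.467 x 0.533 = 0.213; ADM 0.4 x 0.4 x 0.6 + 0.6 x 0.233 x 0.767 = 0.203; sum 0.417.
- Within strata, r = 90%: controls 0.4 x 0.9 x 0.1 + 0.6 x 0.4 x 0.6 = 0.180; ADM 0.4 x 0.45 x 0.55 + 0.6 x 0.2 x 0.8 = 0.195; sum 0.375.
- Ratios: 0.450/0.417 = 1.08 and 0.450/0.375 = 1.20, equivalent to about 8-20% more patients at best.

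**5. What 30% under ADM requires.**
- With 40% irradiated, even if no other ADM patient is reoperated, the irradiated ADM rate cannot exceed 0.30/0.40 = 75%.
- With no ADM benefit in irradiated patients, they alone contribute 0.4 x 0.8 = 32% to 0.4 x 0.9 = 36% of the arm.
- If ADM halves the rate in both groups, the overall rate is 0.5 x 60% = 30%, exactly as planned.
- At a lower irradiated share s, 30% is reachable without any benefit in irradiated patients if the non-irradiated ADM rate is (0.30 - s x r)/(1 - s): about 4-9% at s = 30%, and 15-17.5% at s = 20%.

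**The case against.** **Two stronger readings are tempting.** A reader might infer that the 30% rate ignores radiotherapy. The protocol does not show this: it gives no derivation, its remark on irradiated patients concerns implant reconstruction in general rather than ADM, and equal halving yields exactly 30%. A reader might also infer that the trial will probably be negative. If ADM halved reoperation only in non-irradiated patients, the ADM rate would be 46-48% and Fisher power at 49 per arm 23-17%. That scenario assumes no effect at all in irradiated breasts, which nothing in the protocol states; section 3 cites some evidence of less contracture and fewer revisions with ADM.

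**The inputs are soft.** The 40% is an institutional share. The statement on revisions carries no figure or time horizon, may refer only to irradiated patients with contracture, and sits near a remark about long-term reoperation, whereas the endpoint is at 24 months. Below 75% reoperation there is no tension with 30% even at a 40% share: 0.4 x 0.70 = 28%. Radiotherapy need not be the strongest predictor either, because Appendix 1 counts exchange of a permanent expander for a gel implant, and section 6.4 puts all Group A patients through two stages. All of this stands, and the sizes above are conditional on it.

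**Randomisation protects validity.** Chance imbalance is already covered by the test's error rate and the confidence interval. That stands: the loss is precision and interpretability, not bias.

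**Covariates may be named in the statistical analysis plan.** This is fair, and their absence from 5.4 is not itself the finding. Stratification factors and sample-size assumptions, however, are set in the protocol.

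**More strata make allocation easier to predict in an open trial.** Section 5.3 already lists 5 units x 2 levels, so a swap adds none to the list.

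**Conclusion.** The point holds as a design weakness. As written, the patient-level stratum should be empty, and the radiotherapy status that the protocol itself links to revision is not balanced. Sections 5.3 and 5.2 (item 8) need reconciling in any case.

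The size is moderate: about a 31% chance of a 10-point imbalance, worth roughly 2.5 to 5 points on a planned difference of 30, and at most 8-20% of effective sample size. These figures rest on 40% irradiated and 80-90% of irradiated controls reoperated. The treatment comparison remains unbiased, 98 is right for its inputs, and 30% is attainable. What is missing is a statement of the effect in irradiated patients on which that rate depends.

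**What to change.** - **5.3:** provided the exclusion of neo-adjuvant chemotherapy stands, replace that stratum with radiotherapy planned at randomisation (expected yes or no, from the multidisciplinary treatment plan), and keep unit.
- **5.4, analysis:** include planned radiotherapy in the logistic regression, and not radiotherapy received, which follows randomisation. Report the adjusted difference with its confidence interval beside the Fisher test. The Fisher test alone captures little of the gain.
- **5.4, sample size:** beside the 60% and 30%, state the radiotherapy share and the ADM effect in irradiated patients that are assumed.

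**Cost:** one item on the randomisation form and a few sentences; no extra patients. The list stays at ten strata, but all ten would now be populated rather than five, averaging 120/10 = 12 patients each, so block size needs care because allocation is disclosed. The expectation at the multidisciplinary meeting will misclassify some patients whose radiotherapy is decided after surgery, which brings the gain below the 8-20% ceiling.
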